##### Web-Based Education: Comparator

A web-based learning package is being developed using Articulate software. Content will be written by a study investigator with significant experience working with children with ASD and intellectual disability and their families. The content will be reviewed by autism experts within the Department of Neurodevelopment and Disability, RCH; the Murdoch Children’s Research Institute; and the Department of Paediatrics, University of Melbourne. A consumer representative will also review the content. Modifications will be made from the feedback received. The content will be succinct and will be designed for the learner to complete within 30 minutes. A small number of short multiple-choice questions will be included in the education package to test understanding and application of knowledge.

##### Simulation-Based Education: Training Intervention

A 1.5-hour simulation-based education session, focusing on managing aggression and externalizing behaviors exhibited by a young person with autism in the inpatient setting, is being developed by the study investigators in conjunction with the Simulation Faculty. The RCH Simulation Program curriculum and simulation sessions are designed according to the concepts described by Dieckmann et al [23], utilizing the debriefing framework by Rudolph et al [24]. The simulation scenarios will be reviewed and trialed by members of the Simulation Faculty, with modifications to improve the learning experience made prior to conducting the sessions. The training sessions will be delivered by the Simulation Faculty in the Simulation Centre with assistance from the Code Grey Coordinator. Two separate simulation exercises will be delivered within this 1.5-hour simulation training session.

Participants will be required to complete pre- and posttraining surveys and a follow-up survey 3 months posttraining. Each participant will be asked to create a unique identifier for use in all the surveys, using the first three letters of their first street name followed by the first two numbers of their mother’s birth date.

Nurses randomized in the ward to receive the training intervention will receive the simulation-based training intervention plus web-based training resources. They will be sent an email with instructions on how to access the surveys and the training and the requirements of the study. Participants in this arm will be instructed to complete the web-based training prior to attending the simulation-based education.

Nurses working in the ward randomized to receive the comparator will receive the web-based training resources only. They also will receive an email outlining the requirements of the study with links to the surveys and the training materials.

The intervention arm will be sent an electronic link to reserve their place in one of two simulation training sessions. Each session will have capacity for 5 participants. The comparator arm will be sent a link to access the web-based training. It is expected that the participants will confirm with their Nurse Unit Manager (NUM) whether they are able to be released from ward duties for the duration of the training. Participants will also be instructed via email to complete the pretraining survey prior to commencing the training. The time commitment to complete the web-based education will be 30 minutes, with the simulation education involving a 1.5-hour commitment within working hours.

Staff will complete the simulation training during double staff time; during this time, there are more nurses available to attend training while not compromising patient care. The principal investigator will liaise with the relevant nurse education team members to ensure that nurses have the capacity to complete the simulation-based training and the online training during double staff time. This is the time that education is often scheduled for nurses working on wards. The training was scheduled for late Spring 2019, when it was anticipated that ward activity levels would be lower than during the winter period. The nursing executive and the NUMs of the study wards have agreed to support this study, as have the RCH Simulation Program and the Department of Neurodevelopment and Disability.

##### Training Intervention

A researcher who is not involved with this study will explain the study design to the participants prior to commencement of the prebrief to the simulation training. The researcher will explain that participants will complete a short electronic survey at the completion of the simulation education program. The survey will be completed anonymously with no personal details recorded. The researcher will explain that the simulation sessions will be recorded to enable researchers to view the recordings at a later date to assess the impact of the training on participants’ performances in de-escalating aggressive situations. Only the study investigators will have access to the recordings, which will be deleted once analyzed. The assessment of the recordings will not include any participant identification details. Participants in the simulation-based education intervention will be asked to maintain and hold confidential all information regarding the performance of specific individuals and the details of the specific scenarios. The researcher will check that all participants have completed the pretraining survey. For those who have not, time will be provided for them to complete it in a nearby room with computer access prior to commencing the simulation training.

The Simulation Faculty member facilitating the simulation session will then brief the participants on the objectives of the two simulation exercises. The roles and expectations of both the participants and the instructors will be discussed. The structure of the session and the purpose of the postsimulation debrief will be explained. The participants will be informed that the same professional actor will play the role of the patient in each of the simulation exercises. The second simulation scenario will be more complex than the first, giving the participants the opportunity to extend their skills and build on knowledge learned from the first scenario. Participants will be asked to volunteer for the different roles in each simulation scenario. The Simulation Faculty technologist will orient the participants to the Simulation Centre and simulation equipment prior to commencement of the first simulation scenario.

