#### Interventions

##### Overview

The training intervention will consist of two components:

A web-based learning package, developed using Articulate software (Articulate Global), for the management of aggression and externalizing behaviors in children and young people with autism, with or without intellectual disability, in the hospital setting as prereading.Prereading will be followed by a 1.5-hour simulation-based group education session to manage aggression and externalizing behaviors in an adolescent with autism; this will include two separate simulation exercises, each followed by a facilitated reflective debrief, which explores what the participants did well, what the challenges were, and what they will do differently next time. The first scenario involves an adolescent with autism and aggressive and externalizing behaviors. The second scenario increases in complexity and involves a nonverbal adolescent who has autism and intellectual disability who also demonstrates aggressive and externalizing behaviors. The training will be conducted in the Simulation Centre, conducted by the Simulation Faculty and Code Grey Coordinator, with an actor playing the role of the patient. The parent role in each of the scenarios will be played by a member of the Simulation Faculty. The simulation exercises will be recorded using Sportstec (also known as Studiocode) software.

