##### 1. Pre- and Posttraining Survey (Kirkpatrick Level 1)

A link to a short, electronic REDCap (Research Electronic Data Capture) survey will be administered to participants’ before and after simulation training, incorporating the Confidence in Coping with Patient Aggression Instrument [25], short-answer questions, and free text. These will be used to assess self-perceived levels of confidence and competence in managing aggression as well as the acceptability of the simulation and web-based training.

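### The catch-up rule lets intervention nurses complete the pretraining survey after the web module, so some baselines may already contain part of the training effect

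*Protocol article*

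**What the plan says.** The Protocol article's Overview of the interventions states: "The training intervention will consist of two components". The web package is the first component, as prereading; the simulation session is the second. The section Simulation-Based Education: Training Intervention sets the order for the intervention ward: "Participants in this arm will be instructed to complete the web-based training prior to attending the simulation-based education". The same section gives an email instruction to participants, in a paragraph that covers both arms, to complete the survey before any training: "instructed via email to complete the pretraining survey prior to commencing the training".

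The later section Training Intervention describes the start of the simulation session. "The researcher will check that all participants have completed the pretraining survey", and then: "For those who have not, time will be provided for them to complete it in a nearby room with computer access". This catch-up is timed before the simulation begins, not before the web module.

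The data collection section on the pre- and posttraining survey places the survey link "before and after simulation training". No session, check or catch-up is described for the comparator ward, which receives the web package only.

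**The concern.** A baseline should precede everything whose effect it is meant to help measure. The written fallback allows a nurse who has followed the module instruction to answer the pretraining survey when one of her two training components is already behind her. That component is also the entire treatment of the comparator arm, so a late intervention baseline absorbs the effect that the comparator's own change is meant to show.

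Two results use the baseline. Statistical Methods, Primary Outcomes, compares the proportion with high confidence between arms at baseline and at follow-up by chi-square, using before-and-after data. Secondary Objectives sets a target of 80% of participants reporting increased confidence. The procedure is also one that the pilot could hand on to the larger trial.

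**Working it through.** **Order of events for an intervention nurse**
1. The email asks for the pretraining survey before training starts.
2. She is instructed to complete the web module before the simulation session.
3. At the session, a missing pretraining survey is completed on the spot.
4. The simulation follows.

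A nurse who misses step 1, follows step 2 and uses step 3 has a baseline taken after the module. The section that places the survey around the simulation would accept this baseline as valid; the email instruction would not. These sections conflict for the same nurse.

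**Size, for illustration.** The protocol states no effect size, power or significance level that bears on this, so there is no figure of its own to reproduce.

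From the protocol: 10 nurses per arm (Sample Size); confidence responses dichotomized (Statistical Methods).

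Assumed: true baseline high-confidence proportion p0 = 0.30; posttraining proportion p1 = 0.70, so the true change is 0.40; module effect on that proportion g = 0.10 to 0.30; k of 10 intervention nurses answer after the module; no comparator nurse does.

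- Recorded intervention baseline = p0 + (k/10) × g
- False baseline difference between arms = (k/10) × g
- Apparent intervention change = p1 − p0 − (k/10) × g

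| k of 10 late | False baseline difference (g = 0.10 to 0.30) | Apparent change (true 0.40) |
|---|---|---|
| 0 | 0 | 0.40 |
| 2 | 0.02 to 0.06 | 0.38 to 0.34 |
| 5 | 0.05 to 0.15 | 0.35 to 0.25 |
| 10 | 0.10 to 0.30 | 0.30 to 0.10 |

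If m comparator nurses also answer after the module, with the same g, the baseline difference becomes ((k − m)/10) × g. It is zero when m = k, although both arms' changes are then understated.

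**Would the planned baseline comparison reveal it?** I used a normal approximation for two proportions with 10 per arm, an assumed two-sided 5% level, and counted rejections in the direction of the shift. Largest case, 0.30 against 0.60:
- pooled proportion = 0.45
- null SE = √(2 × 0.45 × 0.55/10) = 0.2225
- alternative SE = √((0.30 × 0.70 + 0.60 × 0.40)/10) = 0.2121
- z = (0.30 − 1.96 × 0.2225)/0.2121 = −0.64, so power is about 0.26

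The smallest case in the table, 0.30 against 0.32, gives about 0.03. A non-significant baseline test would therefore not rule the shift out.

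**The 80% criterion.** If increased confidence is scored by comparing the two surveys across all 20 participants, 16/20 = 80% meets the target and 15/20 = 75% does not. One gain hidden by a late baseline could then change the result. The article does not say how increase is scored.

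**The case against.** The strongest reply is that the catch-up is only a fallback. The default instruction, to both arms, is to answer before training. A nurse who overlooked the survey email may also have overlooked the module, and her survey at the session would then be a proper baseline. The module is instructed, not enforced. The wording that ties the survey to the simulation may be loose shorthand, since that section also serves an arm with no simulation. The study design flowchart is not available here and may show the intended order. All this stands, and it limits the point to a possibility of unknown frequency. It does not remove the written route to a post-module baseline.

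The arms are also less different than they look. Comparator nurses receive survey and training links in one email, with no enforced order described, so they too could answer late. The net difference between arms is unknown. What is specific to the intervention arm is a described step that collects late baselines.

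A reader might infer several stronger things that the document does not support:
- **That half of the training precedes a late baseline.** This is true only as a count of components. By stated time the module is 30 minutes against 90 for the simulation: 30/(30 + 90) = 25%.
- **That a mean change score is biased by so many standard deviations.** The planned analysis dichotomizes and compares proportions, so a standard-deviation scale does not describe it.
- **That the catch-up inflates the completion criterion enough to decide it.** An in-person prompt can raise completion in one arm, but the catch-up concerns one of three surveys, and the article gives no arm-level rates from which to size the effect. Reporting completion by arm is enough.

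**Conclusion.** The point holds in a limited form. The sections on survey timing do not agree, and the catch-up rule permits a baseline taken after the web module. For nurses affected, if the module raises confidence, the recorded baseline is too high and the before-and-after change too small, which works against the intervention. On the assumptions above, the intervention arm's change of 0.40 would appear as 0.38 to 0.34 with two late nurses and 0.35 to 0.25 with five. With none late there is no effect. Neither the number late nor the module's effect can be read from the protocol.

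It would be wrong to conclude that the baseline is in fact not pretraining, or that it does differ between arms; the document shows only that it can. It would also be wrong to conclude that the between-arm comparison at follow-up is biased: that contrast does not use the baseline and is not directly affected. Severity is moderate. The primary objective is feasibility and acceptability, and two wards of 10 nurses each would not give a definitive effect estimate even with perfect baselines.

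**What to change.** **For the procedure and the larger trial.** In both arms, open the web module only after the pretraining survey has been submitted. Reconcile the email instruction, the catch-up rule and the data collection section so that pretraining means before the web module. A link from the survey's final page to the module would do this at almost no cost.

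**For the data already collected.** The Results section says that collection is complete and analysis has yet to start, so there is time to act.
- If survey times are held, and module times are held and can be linked to the self-made identifiers, flag baselines completed after the module. Where module times are lacking, flag those completed on the day of the simulation session.
- Have the flag set by the uninvolved researcher who codes the groups under Blinding. A session-day flag can arise in one arm only, so release it to the analyst after the main comparison is finished.
- Do this before the REDCap data are deleted. The Surveys section under Confidentiality places deletion after analysis, while Data Management speaks of five years' storage; the earlier limit is the safe one.
- Report the confidence change with and without the flagged baselines. Do not set every session-day baseline to missing: some will be valid, and each one lost is 1/10 of the arm.
- Report survey completion separately by arm.

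The cost is a little extra analysis and a slightly smaller sample in the sensitivity analysis.

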#### Outcomes

The primary and secondary outcome measures for assessing the acceptability and feasibility of conducting the training intervention are detailed in the Study Objectives section above.

Two simulation scenarios involving an adolescent with autism, intellectual disability, aggression, and externalizing behaviors will be assessed. Study participants will be asked to complete three surveys: a pretraining survey, a posttraining survey, and a follow-up survey.

The purpose of the pretraining survey is to determine participants’ self-perceptions of confidence and competence in managing aggressive and externalizing behaviors in a young person with autism. The pretraining survey incorporates the Confidence in Coping with Patient Aggression Instrument [25], short-answer questions, and free text to assess self-perceived levels of confidence and competence in managing aggression in a young person with autism and intellectual disability as well as acceptability of the simulation- and web-based education. The Confidence in Coping with Patient Aggression Instrument is a one-dimensional, 10-item instrument demonstrating a high degree of internal consistency (Cronbach alpha=.92) and precision (SE 1.5) [25].

The purpose of the posttraining survey is to determine if the training had an impact on participants’ self-perceptions of confidence and competence in managing aggression and externalizing behaviors in a young person with autism. The posttraining survey also incorporates the Confidence in Coping with Patient Aggression Instrument [25], short-answer questions, and free text to assess self-perceived levels of confidence and competence in managing aggression and externalizing behaviors in a young person with autism and intellectual disability as well as acceptability of the simulation- and web-based education. The purpose of the follow-up survey is to determine if the training had a continued impact on participants’ self-perceptions of confidence and competence in managing aggression in young people with ASD.

Each of the simulation training scenarios will be recorded. The recordings will be analyzed by two clinicians, who are experienced in clinical aggression management, using the EMDABS to assess the influence the training had on participants’ performances in de-escalating aggressive situations. A study investigator will train the clinicians in the use of the tool using the training materials provided by Mavandadi et al [26], providing a clear definition of terms and items and the scoring system. Both clinicians will use the tool on a recording of a practice simulation involving only members of the Simulation Faculty and the study investigator and will discuss decision-making processes to ensure consistency and interrater reliability [27].

Knowledge retention by study participants 3 months posttraining, as well as continued confidence and exposure to clinical aggression, will be assessed via surveys similar in content to the pre- and posttraining surveys. Results from the pretraining, posttraining, and follow-up surveys will be linked using the unique identifiers that the participants created prior to completing the pretraining survey.

Data will be collected at the ward level at each shift for the duration of the study to assess the number of aggressive incidents and rates of successful de-escalations for patients with ASD. A short survey will be emailed to Associate Nurse Unit Managers (ANUMs), as well as to any additional nurses who acted in the roles of ANUM or *nurse in charge of shift*, at the completion of the study to explore the enablers and barriers to collecting this data.

Total change in Code Grey activations will also be assessed in total and at the ward level. We will also record rates of data collection.

#### Participant Timeline

Figure 1 shows the study design flowchart, including participant recruitment and allocation, intervention components, and follow-up.

**Figure 1 figure1:**
[figure not shown]
Study design. EMDABS: English Modified version of the De-escalating Aggressive Behaviours Scale; RN: registered nurse.

#### Sample Size

We plan to recruit 10 staff members to each arm of the study. This sample size, based on our experiences in an earlier study we conducted, is a good size for a pilot and feasibility study to assess recruitment, contamination, and data collection.

#### Recruitment

A study investigator will provide ward-based education about the study, providing clinical nursing staff with information about the study and an opportunity for questions during the double staff time in each ward two times in a 2-3-week period prior to commencement of the study. Hard copies of the study information will also be provided. Following face-to-face information sharing, study information and a request to participate in the study will be forwarded via email to each nurse in the ward by a study investigator. This email will describe the study and outline the participant requirements. It will include a participant information statement and consent form. Two reminder emails will be sent 1 week apart to potential participants to remind them to respond.

The first 10 nurses from each ward who agree to participate in the study and return the consent form will be accepted into the study. Following randomization, participants from each arm of the study will be sent an information email, specific to the group to which they have been randomized, with all the information they require to participate in the study. This email will include links to the relevant resources and surveys as well as links for securing a position into the simulation training and the focus group interviews. Then, 3 months posttraining, all participants will receive an email reminding them to complete the follow-up survey. This email will be resent two times as a reminder to participants. At the completion of the study, participants will receive a letter that provides a summary of the main study findings and thanks them for their participation in the study.

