### Assignment of Groups

#### Allocation

A researcher who is not associated with this study and is not based at the study site will use a coin toss to randomize the wards included in the study to either the training intervention or the comparison group. This will occur once recruitment is complete. The first coin toss will identify which ward is being considered (ie, heads for one ward and tails for the other). The second coin toss will decide whether the selected ward is assigned to the intervention arm or to the comparator arm. Once the wards have been allocated, the study investigator will be unblinded and will individually notify participants via email regarding the arm of the study to which they have been allocated.

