#### Blinding

Blinding for the study investigators and participants will not be possible. To reduce bias, once data are exported to Microsoft Excel, a researcher who is not involved with the study will code the intervention and comparator groups and remove data columns that relate to the intervention group only, so the person conducting the analysis will be blind to group allocation.

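### As described, nurses receive the pretraining survey only after being told their arm, so baseline self-rated confidence is a post-allocation measure

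*Protocol article*

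**What the plan says.** The sequence has to be put together from several sections of the protocol article.

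- **Before the toss (Recruitment).** After ward information sessions, each nurse is emailed a description of the study. Of its contents the article says: "It will include a participant information statement and consent form". No survey is mentioned. The first 10 nurses per ward to return consent are accepted.
- **The toss (Allocation).** An outside researcher randomizes the two wards by coin. On timing: "This will occur once recruitment is complete". The study investigator is then unblinded and "will individually notify participants via email regarding the arm of the study to which they have been allocated".
- **After the toss (Recruitment).** "Following randomization, participants from each arm of the study will be sent an information email, specific to the group" concerned. On its contents: "This email will include links to the relevant resources and surveys as well as links for securing a position into the simulation training".
- **By arm (Simulation-Based Education: Training Intervention).** Of nurses in the intervention ward: "They will be sent an email with instructions on how to access the surveys and the training and the requirements of the study". Nurses in the comparator ward likewise get an email with survey and training links.
- **Timing rule for the survey.** The same section asks only that the pretraining survey be done before training starts. The Training Intervention section lets simulation participants who have not done it complete it on the day of the session.
- **Blinding.** "Blinding for the study investigators and participants will not be possible". The stated safeguard is that groups are coded by an uninvolved researcher, so that the analyst is blind.

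**The concern.** The pretraining survey measures how confident and competent nurses feel (Outcomes). A self-rating of this kind can be influenced by knowing which training one is about to receive. A baseline taken before allocation cannot be influenced in that way. A baseline taken afterwards can.

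The baseline is used in two ways. Statistical Methods (Primary Outcomes) compares the proportion with high confidence between arms at baseline and at follow-up. Secondary Objectives sets a target of 80% of participants reporting increased confidence, for which the pretraining rating is the natural reference. If knowledge of the arm shifts the starting point, both the baseline comparison and the apparent change carry that shift.

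The order also affects early leavers. A nurse who withdraws on hearing the allocation, before opening the survey, contributes no baseline ratings, so her starting confidence cannot be compared with that of nurses who stayed.

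**Working it through.** No stated figure depends on this point: the 10 per arm rests on the investigators' earlier experience, not on a power calculation. The check is of the order of events, with a little arithmetic for scale.

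**1. Order of events**

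| Step | Event | Section | Survey access described? |
|---|---|---|---|
| 1 | Ward information sessions, hard copies | Recruitment | No |
| 2 | Email with information statement and consent form, two reminders | Recruitment, Consent | No |
| 3 | First 10 consenting nurses per ward accepted | Recruitment | No |
| 4 | Coin toss, after recruitment closes | Allocation | No |
| 5 | Individual notification of arm | Allocation | No |
| 6 | Arm-specific email | Recruitment; Simulation-Based Education: Training Intervention | **Yes, both arms** |
| 7 | Pretraining survey, any time before training | Simulation-Based Education: Training Intervention; Training Intervention | Completed here |

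The only contact said to give survey access before training is step 6, which is specific to the arm. That the link is not sent earlier is an inference from all the contacts described. No sentence says so outright, and Figure 1 is not available to confirm it.

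**2. Does the stated safeguard cover this?** No. Analyst blinding acts after the data are exported. It cannot change a rating already given by a nurse who knew her arm.

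**3. Is completion handled alike in both arms?** Supervised time to finish a missing pretraining survey is described only for the simulation session, so timing and completeness of baseline could differ by arm.

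**4. Scale (illustration only).** Input: 10 nurses per arm (Sample Size).

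- One nurse crossing the high-confidence cut: 1/10 = 10 percentage points on that arm's baseline.
- Assumed example: true baseline 5/10 in each arm, and three nurses in one arm rate themselves below the cut because they know their arm. The arms then read 2/10 and 5/10, a 30-point gap. Pearson chi-square without correction = N(ad − bc)² / (product of margins) = 20 × (2×5 − 8×5)² / (10 × 10 × 7 × 13) = 18,000 / 9,100 = 1.98, p = 0.16. A gap of that size would not reach significance at the conventional 5% level (my assumption; the article states no alpha).

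**5. Early loss.** The Outcomes criteria under Primary Objective require attrition below 20%. Of 20 nurses, 3/20 = 15% meets this and 4/20 = 20% does not, so at most 3 may be lost. Three is therefore a ceiling on nurses without a baseline if the criterion is met, reached only if every loss came on disclosure and before the survey.

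**The case against.** The strongest case on the other side has five parts.

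- **The timing is inferred.** The rule that the survey precede training does not exclude completion before the toss, and Figure 1 might show it. This stands as a caveat. It does not overturn the reading, because each email said to carry survey links is the arm-specific one.
- **The bias is conjectural.** This stands as to direction and size. A reader might infer that nurses allocated to simulation would mark themselves down because they had been told they would be tested on camera. The documents do not support that: recording is explained at the session itself, the allocation email is not said to mention it, and testing is not how the article describes the session. What is established is that the ratings are exposed to knowledge of the arm.
- **Losses remain countable.** A reader might infer that attrition by arm could not be described. It could: consent precedes the toss, 10 nurses per ward are accepted, and ward determines arm, so each arm's denominator is known. Nor do all leavers lack a baseline; a nurse who answers and then leaves has one.
- **Little turns on it in this pilot.** The primary objective is feasibility and acceptability, and increased confidence is a secondary objective. This is largely fair, although Statistical Methods places the confidence comparison under primary outcomes.
- **Reordering cannot rescue the between-arm comparison.** With one medical and one surgical ward, any baseline gap is inseparable from ward differences, and later ratings stay unblinded. This stands in full. The gain is a reference rating free of allocation knowledge, not an unconfounded comparison.

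**Conclusion.** The point holds as a modest, avoidable weakness in the order of procedures. On every contact the article describes, baseline self-ratings are collected after allocation is disclosed, and analyst blinding does not address this. The conclusion assumes that Figure 1 and the full protocol place no survey before the toss.

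The size of any bias is unknown. The 10 points per nurse is a consequence of having 10 nurses per arm, and would apply to any cause of a changed answer; neither it nor the 30-point example estimates what happened. The limit of 3 nurses without a baseline is likewise a ceiling, not an expectation.

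A reader might also infer that nurses were recruited knowing their arm. They were not: recruitment and consent close before the toss. The weakness is confined to baseline measurement and to the missing ratings of nurses who leave before answering.

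**What to change.** **For the larger trial**, change the order as follows.

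1. Send the pretraining survey link to each accepted nurse (the first 10 per ward) on receipt of consent. Limiting it to accepted nurses avoids surveying those who consent after the places are filled.
2. Add a ward item to that survey. Responses are anonymous and linked only by a self-made identifier, so without it a survey taken before the toss could not be assigned to an arm. The uninvolved researcher who codes the groups can recode this item, so that the analyst stays blind.
3. Amend Allocation so that the coin toss takes place once recruitment is complete and the accepted nurses' pretraining surveys have been submitted, or a stated closing date has passed.
4. Keep only the training, posttraining and follow-up links in the post-randomization email.

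**For this pilot**, the Results section says data collection ended in February 2020, so the order cannot be changed. The report should state that baseline was collected after allocation was disclosed (if Figure 1 and the study records confirm this), give the number per arm with no pretraining survey, and interpret change in confidence accordingly.

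**Cost.** Emails are reordered and one item is added; no extra survey round, staff or participants are needed. The gap between baseline and training becomes slightly longer, and the toss waits briefly for outstanding surveys. A closing date still allows some missing baselines, but any nurse missing at that point is missing for reasons unrelated to knowing the arm. The change does not remove the confounding of arm with ward or unblind-proof the later ratings.
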